### Variables measurement

2.8

Socio-demographic variables will be collected: gender, age, education, usual residence, *per capita* monthly income of the family, mode of bearing medical expenses, and clinical information such as duration of DTC, detailed medical history.

Physiological Indicator Variables: TSH will be detected using radioimmunoassay (RIA), the medical staff will clean the patient’s blood collection site using a sterilized cotton ball, and then use a needle to take an appropriate amount of fasting venous blood 5 mL, centrifuged at 3000 r/min for 5 min, serum will be separated, and a certain amount of TSH antibody labeled with the radioisotope iodine-125 will be added to the processed serum to bind to the TSH to be detected. TSH. Using biochemical techniques, the antibody-bound TSH and unbound free TSH were separated into solid phase and free phase. The radioisotopes in the solid phase are measured to obtain a corresponding count value, from which the concentration of TSH in the sample can be determined. Based on the stratification of risk factors for recurrence of differentiated thyroid cancer, patients can be categorized into low-risk, intermediate-risk, and high-risk strata, and postoperative serum TSH target values are set accordingly (56). In general, the division is based on factors such as age, gender, tumor stage, presence of lymph node metastasis, and type of thyroid cancer variant. All patients included in this trial were high-risk patients treated with iodine 131, and according to treatment guidelines, for high-risk patients, postoperative serum TSH should be suppressed to very low levels (<0.1 mIU/L) or completely suppress thyroid function to minimize the risk of recurrence. Therefore, the TSH compliance rate was defined as postoperative serum TSH < 0.1 mU/L, and this criterion was used to calculate the TSH compliance rate.

T4, T3, FT3, and FT4 will be measured by enzyme-linked immunosorbent assay (ELISA). The medical staff will clean the patient’s blood collection site using a sterilized cotton ball, and then use a needle to take a tube of appropriate amount of fasting venous blood of 5 mL, respectively, to prepare the required reagents, including enzyme-labeled antibody, substrate, and washing buffer. At the same time, prepare the sample to be tested. Fix the specific antigen or antibody on a microtiter plate, usually using a multiwell plate, such as a 96-well plate. Add enough antigen or antibody solution to each well and incubate at a constant temperature so that it adsorbs to the well walls. The samples to be tested are pretreated as necessary, e.g., dilution, protein cleavage. The pre-treated samples or standards are added to each well. A series of standard curve samples of varying concentrations are usually set up and used to generate a standard curve to calculate the concentration of the target in the sample to be tested. Enzyme-labeled antibodies conjugated to the target are then added and incubated. The samples and unbound material in the wells are washed away to minimize non-specific binding. An appropriate substrate is added to react with the enzyme-labeled antibody. The choice of substrate depends on the enzyme marker used, commonly horseradish peroxidase (HRP) used in ELISA. After an appropriate period, the reaction is terminated by the addition of a reaction stopping solution and prevented from producing further color changes. The absorbance values of each well are read using an enzyme meter or photometer. Based on the standard curve, the concentration of the target in the sample to be tested is calculated.

Sociodemographic variables will be collected from patients at baseline. Clinical reagent testing and questionnaires will be completed at baseline as well as at 3 and 6 months of follow-up, with data collection times shown in Table 2.

**Table 2 tab2:** Data collection components and collection timeline.

Type of research	Data collection component		Timepoint		
			0 M	3 M	6 M
Quantitative research	Sociodemographic variables	Sex, age, social insurance status, place of residence, average monthly household income, educational level, area of domicile, clinical information	√		
	Anthropometric variables	Thyroid stimulating hormone (TSH), thyroxine (T4), triiodothyronine (T3), Free T3, Free T4	√	√	√
	The MTM theory scale	Questionnaire: Changes measured by the MTM Theory Scale	√	√	√
	Tthe frequency of iodine-containing diets	Questionnaire: Changes in the frequency of iodine-containing diets	√	√	√
	Medication adherence	Questionnaire: Medication Refill or Medication Adherence Scale (ARMS-7)	√	√	√
	Quality of life	Questionnaire: EuroQol-5 Dimensions 5 Levels(EQ-5D-5 L7)	√	√	√
	Satisfaction	Questionnaire: Customer Satisfaction Questionnaire (CSQ-3)	√	√	√
	Depression and anxiety	Questionnaire: Simplified version of the Anxiety Depression Scale (PHQ-4)	√	√	√
	Fear of cancer recurrence	Questionnaire: Fear of Cancer Recurrence Scale (FCR-4)	√	√	√

### Questionnaires

2.9

Changes in self-management behaviors will be assessed by a self-designed MTM scale (57) consisting of 6 dimensions including PD, BC, CPE, ET, PC, and, CSE using a 5-point Likert scale design, the scale will be developed and final validation will be completed by the researcher, and 20 randomly selected participants who did not take part in the final trial will complete a pre-test from the recruited participants to determine the appearance validity and the content validity through pre-testing and expert testing to refine the model scale.

Changes in the frequency of iodine-containing diets will be assessed by patients through a self-administered the Iodine-containing Food Frequency Questionnaire (I-FFQ) questionnaire after adaptive adaptation and refinement based on the Food Frequency Questionnaire (FFQ) (58, 59). Preparation will be done in consultation with experts and based on food guidelines, several foods likely to be consumed on a daily basis with an iodine value greater than 400 mg/kg (60, 61), including iodized salt, will be selected as the target for measurement, and the time scale will be measured as the basis for frequency (62).

Medication adherence will be measured using the Renewal or Medication Adherence Scale (ARMS-7), which has seven entries and two dimensions: medication adherence (entries 1–4) and refills (entries 5–7), which is a 4-point Likert scale ranging from 1 (none) to 4 (all), notably one entry in the scale (the seventh) is reverse scored (1 = all to 4 = none). It measures self-reported medication adherence with respect to both taking medication as prescribed and taking medication as scheduled. The total score was derived by summing the responses to all items. The total score ranges between 7 and 28, with higher scores being associated with lower medication adherence. The scale has high validity and reliability in measuring medication adherence, with total scale item correlation coefficients ranging from 0.35 ~ 0.58 and a Cronbach’s alpha of 0.75 (63).

Quality of life will be assessed using the EuroQol-5 Dimensions 5 Levels (EQ-5D-5L), which is an improved version of the EQ-5D that introduces five tiers (64, 65) on top of the original five dimensions, (eg. no difficulty, minor difficulty, moderate difficulty, major difficulty, total difficulty) thus providing a more refined health status Assessment. Its health utility values ranged from 0.62 to 0.90 in seven studies reporting cancer patients with high validity and reliability (66–72). Compared to the traditional EQ-5D (EQ-5D-3L), the dimensional and hierarchical structure of the EQ-5D-5L remains unchanged, but the number of ratings for each dimension has been increased to five. The five dimensions of the EQ-5D-5L include Mobility (Mobility), Self-care (Self-care), Usual activities (Usual activities), Pain/Discomfort, and Anxiety/Depression. For each dimension, the individual selects the appropriate level according to his or her situation, thus constituting a five-dimensional description. In addition to the five-dimensional descriptors, the EQ-5D includes a Visual Analog Scale, which allows individuals to give a subjective rating of their current state of well-being based on their feelings on a scale of 0 to 100. This score provides a continuous variable to measure an individual’s overall quality of life.

Satisfaction will be adapted using the Customer Satisfaction Questionnaire (CSQ-3), which is a commonly used customer satisfaction questionnaire for assessing customer satisfaction with a product, service, or experience, with a Cronbach’s alpha of 0.84, and good reliability and validity (73, 74). The CSQ-3 is a revised version of the CSQ which was developed by Roger, D et al. in 1993 and has been widely used in the fields of market research, customer relationship management, and business decision making (75, 76). This question is designed to assess the customer’s level of satisfaction with the overall product, service, or experience. Response options are usually on a five-point scale from very dissatisfied to very satisfied. The CSQ-3 is designed to be simple and straightforward and is suitable for quickly gathering information on customer satisfaction.

Depression and anxiety will be assessed using a simplified version of the Anxiety Depression Scale (PHQ-4), which is a short, self-report scale used to assess an individual’s symptoms of depression and anxiety over the past 2 weeks, and consists of two dimensions of depression as well as anxiety, with a total of four entries, the first two of which relate to depressed mood and the last two to anxiety (77). Each entry was rated on a 4-point scale, with “not at all, ““a few days,” “more than half the days,” and “almost every day,” corresponding to 0, 0, and 0, respectively. Each entry is rated on a 4-point scale, with “not at all,” “a few days,” “more than half the days,” and “almost every day” corresponding to a score of 0, 1, 2, and 3, respectively, and the total score ranges from 0 to 12. The Cronbach’s alpha of the PHQ-4 was 0.833, which is of high validity and reliability, in a study conducted in China (78). The PHQ-4 scale is very concise, and it is easy to use and comprehend. It can help healthcare professionals to quickly screen individuals with symptoms of anxiety and depression and provide an initial assessment.

Fear of cancer recurrence will be assessed using the Fear of Cancer Recurrence Scale (FCR-4) (79). The FCR-4 scale is a simplified version based on the “FCR-7” scale, developed by Simard and Savard in 2018, with a measured Cronbach’s alpha of 0.86 (80). The FCR-4 consists of four questions to assess the level of fear of cancer recurrence among cancer patients. Recurrence and is usually rated on a five-point Likert scale from completely disagree to completely agree. The use of the FCR-4 scale can help healthcare professionals to understand the level of fear cancer patients have about cancer recurrence and provide them with appropriate support and mental health resources. This information can be used in the development of individualized treatment plans to help patients cope with their fears and improve their quality of life.

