#### Intervention group: online MTM-based health education

2.5.1

The intervention group receives MTM-mHealth, and the realization of health education will rely on the smart terminal WeChat platform. Combined with the chat communication function of WeChat, timely communication between physicians and patients will be realized, and patients’ concerns will be answered by physicians or professional nurses in a timely manner. At the same time, through the WeChat platform, physicians or professional nurses can realize timely interventions for patients, including daily reminders of medication taking, popularization of thyroid cancer-related science, and interpretation of cutting-edge research on thyroid cancer.

The intervention group had WeChat group health education, online health education lectures, received routine medical care such as health education program and medication supervision on the day of hospitalization, then received treatment in the outpatient clinic, and received intervention in mobile health education after discharge for 3 months, and the content of the intervention was designed based on the theory of MTM, and the flowchart is shown in Figure 2.

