##### Participatory dialog (when strengths outweigh weaknesses)

2.5.1.1

Purpose: to motivate patients to start behavioral change, so that patients produce initial action self-efficacy.

Measures: Give each patient a copy of the booklet “Health Education for Thyroid Cancer Patients.” While distributing the education booklet, the physician explains and emphasizes the common problems of the patients, encourages the patients to face the disease positively, and guides the patients to consciously improve their own health behaviors. During the first visit, patients and physicians ask each other questions as much as possible, encouraging patients to actively participate in the initial patient-physician communication. At the same time, the physician added the patient’s WeChat contact information, in order to further provide timely health education to the patient.

After the patient is discharged from the hospital, the physician and the patient regularly communicate with each other through the online doctor-patient salon at 9:00 a.m. on Saturdays, the content of the communication includes disease cognition, prognosis and development, etc., and the link includes the physician’s explanation, the physician-patient Q&A, and the patient–patient communication, etc., and the physician needs to guide the patient to explore the advantages and disadvantages of improving the self-health behaviors on the recovery of the disease, and the physician needs to emphasize that the advantages of the self-health behaviors outweigh the disadvantages so that the patient The physician should emphasize that the advantages of self-health behaviors outweigh the disadvantages, so that the patient can actively participate in the joint decision-making process.

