##### Behavioral confidence (belief in one’s ability to achieve desired behaviors)

2.5.1.2

Purpose: to enhance patients’ confidence in changing health behaviors in the future.

Measures: Physicians and relevant nursing staff set up a doctor-patient exchange group on WeChat, grouping patients according to the initial treatment ward and electing a group leader, who organizes regular exchanges between patients, with the group leader deciding the time of exchanges himself/herself. Physicians and related nursing staff encouraged and instructed all patients to fill out a “health behavior diary” to record the daily maintenance of health behaviors and problems and experiences encountered during the process, and to share and exchange them in the WeChat group every day. At the same time, patients were encouraged to communicate with their physicians in a timely manner, and the physicians evaluated the progress of the patients’ health behaviors in a timely manner. With half a month as a cycle, physicians or relevant nursing staff after evaluation and comparison, the merit of inviting patients who maintain good health behavior to present themselves, in the form of WeChat group to open a patients’ club, the patients through the group learning and communication, sharing daily experience, discussion, interaction and mutual learning.

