### Outcomes

2.7

Primary Outcome: Change in TSH from Baseline and at 3 and 6 Months Follow-Up.

Secondary outcomes:

changes in self-management behaviors: changes measured by the MTM Theory Scale, changes in frequency of iodine-containing diets, medication adherence.Social cognitive and psychological: quality of life, satisfaction, depression, anxiety and fear of cancer recurrence.Metabolic control: thyroxine (T4), triiodothyronine (T3), FT3, FT4.

The corresponding study questionnaires completed by all patients at baseline as well as at follow-up were piggybacked on a web-based platform (Questionnaire Star). Clinical pharmacists distributed the questionnaires via Questionnaire Star, and patients were instructed to fill them out by pharmacists either face-to-face (during hospitalization) or by telephone (after discharge). Patient demographic information was collected through the case system and self-designed questionnaires.

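### Change on the self-designed MTM scale is labelled change in self-management behaviour, but its six dimensions are determinants of behaviour and match the six intervention modules one to one

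*Protocol article*

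**What the plan says.** Section 2.7 (Outcomes) opens its secondary outcomes with "changes in self-management behaviors: changes measured by the MTM Theory Scale", followed under the same item by the frequency of iodine-containing diets and by medication adherence. Section 2.9 (Questionnaires) repeats the label: "Changes in self-management behaviors will be assessed by a self-designed MTM scale". It describes the instrument as "consisting of 6 dimensions including PD, BC, CPE, ET, PC, and, CSE using a 5-point Likert scale design".

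On development it says that "the scale will be developed and final validation will be completed by the researcher". It plans a pre-test in 20 people who stay outside the final trial, "to determine the appearance validity and the content validity through pre-testing and expert testing to refine the model scale".

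On the intervention, section 2.5.1 says that "the content of the intervention was designed based on the theory of MTM". Sections 2.5.1.1 to 2.5.1.6 then set out one module per MTM construct. The second, for example, is headed "Behavioral confidence (belief in one’s ability to achieve desired behaviors".

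The second specific objective, at the end of section 1, is whether the MTM programme improves the self-management skills of these patients.

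**The concern.** An outcome called behaviour should measure behaviour. Here the named instrument measures the constructs through which the theory says behaviour is changed, and the intervention is built from those same constructs. Only one arm receives the six modules. Patients in that arm could report more dialogue, more confidence, better access to resources or more social support without taking levothyroxine more reliably or eating less iodine.

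What is at stake is the meaning of a positive result for the second objective. Section 3 compares change in scale scores between the arms at a two-sided 0.05 level. Under the present labels, a significant MTM difference could be reported as improved self-management behaviour while medication adherence and diet stayed flat.

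**Working it through.** No arithmetic applies: the plan gives no figure for this scale. The sample size in section 2.3 is built on the TSH achievement rate and does not depend on this point. The check is a comparison of sections.

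**Step 1. Match the scale's dimensions to the modules and to their role in the theory.**

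| Scale dimension (2.9) | Intervention module | Role given in section 1 |
|---|---|---|
| PD | 2.5.1.1 Participatory dialog | influences initiation |
| BC | 2.5.1.2 Behavioral confidence | influences initiation |
| CPE | 2.5.1.3 Physical environment | influences initiation |
| ET | 2.5.1.4 Emotional transformation | influences maintenance |
| PC | 2.5.1.5 Practice change | influences maintenance |
| CSE | 2.5.1.6 Social environment | influences maintenance |

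The match is 6 of 6. In section 1 all six are factors acting on behaviour change.

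**Step 2. See what the article itself calls behaviour.** Section 1 treats self-management as what patients do about exercise, diet, routine and medication, and defines health behaviours as actions. Section 2.1 gives medication use and diet as its examples of self-management behaviour. None of the six dimensions is named for any of these. The label in 2.7 and 2.9 therefore conflicts with the article's own usage in sections 1 and 2.1.

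**Step 3. Ask whether the described validation would separate the two.** Section 2.9 plans face and content validity, from a pre-test and expert opinion. Neither compares the score with medication taking or diet, so neither could show that a higher score means changed behaviour.

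**Step 4. Compare the arms.** Under section 2.5.2 the control arm gets discharge education, an education booklet and monthly telephone calls. It does not get the salons, WeChat groups, diaries, scheduled educational material or daily reminders that make up the modules. Exposure to the constructs differs by design.

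**Step 5. Count what is affected.** The outcome lists three measures: the MTM scale, iodine-diet frequency (I-FFQ) and medication adherence (ARMS-7). One of the three is affected. Table 2 schedules the other two at 0, 3 and 6 months, so more direct measures are already in place.

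**The case against.** The strongest reply is that much of this is inferred from dimension names. No items are shown and the scale is still to be developed. A Likert item under a given dimension might ask about exposure, about confidence or about actual conduct. This stands: the overlap is at dimension level. A reader might infer that the score simply measures what the intervention arm was taught; the article does not support that, only that it may.

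Second, a reader might infer that the second objective will be decided on the MTM score, because it is listed first. The article states no such rule, and order in a list is not a hierarchy. What stands is narrower: nothing in the stated labels prevents that reading of a positive MTM result.

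Third, the line between determinant and behaviour is not perfectly clean. Section 2.5.1.5 describes practice change as evaluating and adjusting one's own efforts, which is close to self-regulatory conduct, and the objective speaks of skills. This softens the point for one dimension of six. It does not rescue the label, since 2.7 and 2.9 say behaviours.

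Fourth, the contrast between the arms is not all or nothing. The control booklet has almost the same title as the one given in the first module, and the monthly calls add contact. The intervention lasts 3 months, so the 6-month score is taken after exposure has ended. Both facts weaken the exposure explanation, the second at 6 months in particular. Neither turns a determinant into a behaviour.

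Fifth, ARMS-7 and I-FFQ have a related weakness. Both are self-reported, the I-FFQ is adapted for this study, and the intervention arm is prompted on medication and iodine intake. This stands as a limit on the remedy. The two instruments still ask about the behaviours themselves, which the MTM dimensions do not.

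Measuring the constructs of the guiding theory is sound in a theory-based trial. The objection here is to the label, not to collecting the scale.

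**Conclusion.** The concern holds as a mislabelled secondary measure. The article's own account of the theory places all six scale dimensions among the influences on behaviour, its own examples of behaviour are medication use and diet, and the six dimensions match the six modules. A rise in MTM score may therefore show exposure to the programme or a shift in determinants rather than changed behaviour.

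Its size is one of three measures under one secondary outcome, with a bearing on one of the two stated objectives. The primary outcome is a laboratory value and is not affected. The likely inflation of the MTM score cannot be quantified from the article.

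The conclusion assumes that the items follow the dimension names. If the final items turn out to ask about medication taking or diet directly, the point weakens to that extent.

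**What to change.** In sections 2.7 and 2.9:

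- Keep the MTM scale at all three visits, but classify it as a theory-construct (process or mediator) measure, separate from the behaviour outcomes.
- Rest the conclusion on self-management behaviour on ARMS-7 and I-FFQ.
- State that a change in MTM score alone does not show improved self-management behaviour.
- Say that ARMS-7 and I-FFQ will be read alongside TSH, because both are self-reports of behaviours on which the intervention arm is prompted.

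The cost is wording only. No data, visits or sample size change. The downside is one fewer outcome supporting the second objective, which would then rest on two self-reported measures with TSH as the laboratory counterpart.
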